**Enrollment failure**
Enrollment failures are not expected as patients, who are willing to participate and are vaccinated according to the recent version of the COVID-19 vaccination standard [20], are all included in the study.A minimum set of enrollment failure information is required. Minimum information includes date of informed consent, demography, enrollment failure details, eligibility criteria, and information on any solicited adverse events or serious adverse events that may have occurred from the time informed consent was obtained to the time of withdrawal.

### Visits and Study-Related Assessments

Visit details are listed in Textbox 4 and Table 1. The visit schedule is displayed in Table 1.

Visits and study-related assessments
**Visit 1**
Following assessments will be performed at this visit:Review of inclusion and exclusion criteriaWritten informed consent will be obtainedDemographics including age and sex will be obtainedRelevant medical history including all prior chemotherapy regimens and radiation therapy will be collectedCollection and review of previous and concomitant medicationSARS-CoV-2 antigen test obtained from nasal, pharyngeal, nasopharyngeal, or oropharyngeal swabPatient diary will be handed out and explained to the patient. Patient is instructed to record solicited adverse events that occur within 7 days after the time of vaccination in the patient diary (the day of vaccination plus the following 6 days)Prevaccination blood sampling for SARS-CoV-2–specific B- and T-cell immune response assessment will be performed (maximum 36 mL blood)
**All following visits**
Review of any changes of concomitant medication since the last visit and documentation in the electronic case report form if applicableReview of patient diary and documentation of adverse events (see safety)Prevaccination blood sampling for SARS-CoV-2–specific B- and T-cell immune response assessment will be performed (maximal 18 mL blood)
**Follow-up visits**
Days in the follow-up period are counted from the day of the last vaccination onward. The visit schedule is displayed in Table 1.
**Follow-up visit 1**
The following assessments will be performed at this visit:Collection of patient diary and documentation of adverse events (see Safety section for details). The patient diary will remain at the study site together with the patients’ medical recordsBlood sampling for SARS-CoV-2–specific B- and T-cell immune response assessment (maximal 18 mL blood)
**All following follow-up visits**
The following assessment will be performed at all subsequent follow-up visit:Blood sampling for SARS-CoV-2–specific B- and T-cell immune response assessment (maximal 18 mL blood)Previous and concomitant medication of interestInformation on previous and concomitant immunosuppressive medication within 90 days prior to providing informed consent will be recorded in the electronic case report form. In addition, all COVID-19 vaccinations and all therapeutic neutralizing antibodies against SARS-CoV-2 (tixagevimab-cilgavimab, sotrovimab, convalescent plasma, etc) a patient has ever received will be documented in the electronic case report form.

**Table 1 table1:** Visit schedule.

Procedures	Vaccination period		Follow-up period	
	Visit 1	All following visits^a^	FU^b^ 1	All following FUs
Day^c^	0^c^ (42^d^)	28-day intervals^c,d^	28^e^	28-day intervals^e^
Visit window (days)	±5	±5	±5	±5
Informed consent	✓			
Demographics	✓			
Review of inclusion and exclusion criteria	✓			
Medical history	✓			
Concomitant medication	✓	✓	✓	✓
SARS-CoV-2 antigen test	✓			
SARS-CoV-2–specific B- and T-cell immune response^f^	✓	✓	✓	✓
Dispensing of the study diary	✓			
Collection of the study diary			✓	
Review of diary and documentation of solicited adverse events^g^		✓	✓	
Complete case report form	✓	✓	✓	✓
Standard cellular immunity^h,i^	✓	✓	✓	✓
SARS-CoV-2 Quantiferon^i^	✓	✓	✓	✓
Omicron-BA.1–specific nAB^i,j,k^	✓	✓	✓	✓
Anti-spike-1/2 IgG^l^ antibodies^i,j^	✓	✓	✓	✓
Anti-nucleocapsid IgG^l^ antibodies^i^	✓	✓	✓	✓
Anti-SARS-CoV-2 vaccination^i^	✓	✓		

^a^Visit only in case anti-spike-1/2-IgG titer was <847 BAU (binding antibody units)/mL at the previous visit according to standard-of-care COVID-19 vaccination.

^b^FU: follow-up.

^c^Day 0 is the day of the first visit and first vaccination. All days in the vaccination phase are counted in relation to the last vaccination, respectively.

^d^Applicable for patients posthematopoietic stem cell transplantation (HSCT) or chimeric antigen receptor (CAR)–T cell treatment. Day 0 is considered the day of HSCT or CAR-T cell treatment. All days in the vaccination phase are counted in relation to the day of HSCT or CAR-T cell treatment, respectively.

^e^Days in the follow-up phase are always counted in relation to the last vaccination.

^f^Maximum 36 mL blood is collected at visit 1. At all other visits, maximum 18 mL blood is collected.

^g^Solicited adverse events will be documented for 7 days after each vaccination.

^h^Contains blood cell count, T-lymphocytes (CD3, CD4, CD8), natural killer cells (CD16+56), B-lymphocytes (CD19), and activated T cells (CD38, HLA-DR).

^i^Performed as part of the COVID-19 vaccination standard [20] in the clinical routine. Data generated within the standard procedures will be used for analysis of the study objectives.

^j^Anti-spike-1/2 IgG titer ≥33.8 BAU/mL was interpreted as reactive, according to the manufacturer’s instructions (DiaSorin). To determine Omicron BA.1-specific neutralizing serum titers, the lowest tested serum dilution was 1:30, which served as the lower limit of quantification.

^k^nAB: neutralizing antibody.

^l^IgG: immunoglobulin G.

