**Exclusion criteria**
Patient is not vaccinated according to the recent version of the COVID-19 vaccination standard [20]Patient has a positive SARS-CoV-2 antigen test at the first visit

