### Statistical Considerations

The primary analysis set comprises all enrolled patients who received at least one vaccination within the COVID-19 vaccination standard [20]. The statistical analysis is essentially descriptive and focuses on estimation of the time to event, that is, primary and secondary end points. The event-time distributions are described by the Kaplan-Meier method [24] with pointwise 95% confidence bounds [25] (18, “log-log”). Relevant percentiles (eg, quartiles) with 95% CIs are derived. Generally, quantitative variables are summarized by mean, SD, and percentiles (0, 25, 50, 75, 100), and qualitative variables by absolute (ie, count) and relative (ie, percentage) frequencies. Extreme values (“outliers”) are flagged and listed.

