### Sample Size

The target sample size of 100 is sufficient to estimate event-free probabilities around the median “survival” with acceptable precision (half-width of a 95% CI) of about 10% for censoring rates less than 20% (Table 3).

**Table 3 table3:** Sample size calculation.

Number of events	Half width^a^ (%)
100	9.7
90	9.9
80	10.2
70	10.6
60	11.1
50	11.8
40	13.3
30	15.4
20	19.7
10	21.7
0	—^b^

^a^“Absolute” percentage points.

^b^Not applicable.

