### Limitations

This study design has several a priori limitations. The study focuses on COVID-19 vaccination only. Patients with SARS-CoV-2 infection are excluded when tested positive; however, studies have shown that SARS-CoV-2 infections also induce immune responses and therefore increase protection [26]. Future study results have to be interpreted cautiously due to the potential risk of bias as data are collected as part of an observational study and in the frame of a SOC COVID-19 vaccination schedule. Patients therefore are not randomized. Further, potential confounders are not included in the statistical analysis.

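### The secondary response and waning end points count any titer crossing after vaccination, whatever its cause; a second analysis that sets infection and passive antibody apart should be prespecified

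*Protocol article*

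**What the plan says.** **End points.** Textbox 2 of the protocol article sets four secondary end points: time to anti-spike IgG of at least 33.8 BAU/mL, time to a BA.1 ID50 titer of at least 30, and time to falling below each level after the last vaccination. They are tied to vaccination by timing only. The primary end point is time to an adequate immune response under the vaccination standard; its definition is in Multimedia Appendices 1 and 3, which are not shown.

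**Analysis.** Under Statistical Considerations the primary analysis set is "all enrolled patients who received at least one vaccination within the COVID-19 vaccination standard", and "The event-time distributions are described by the Kaplan-Meier method [24] with pointwise 95% confidence bounds". The Limitations note that infection also induces immune responses, and then state: "Further, potential confounders are not included in the statistical analysis".

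**Safeguards.** One exclusion criterion concerns infection: "Patient has a positive SARS-CoV-2 antigen test at the first visit". Textbox 3 also requires withdrawal of a patient who already has an adequate response at the first visit.

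**Data collected.** Table 1 schedules "Anti-nucleocapsid IgG" at every vaccination and follow-up visit, with concomitant medication reviewed at each. Textbox 4 adds that "all therapeutic neutralizing antibodies against SARS-CoV-2 (tixagevimab-cilgavimab, sotrovimab, convalescent plasma, etc) a patient has ever received will be documented". Footnote i of Table 1 says that routine data of this kind will be used for the study objectives, without saying how.

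**The concern.** The study is meant to describe the immunogenicity of a vaccination standard and to inform vaccination and booster schedules. Infection can lift both anti-spike IgG and BA.1 neutralization. Convalescent plasma or a therapeutic anti-spike antibody can lift binding IgG. The Introduction says that therapeutic monoclonals lost neutralizing capacity with Omicron, so that route bears mainly on the binding end points.

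The two safeguards act at visit 1. Neither covers an infection or infusion after that visit. The withdrawal rule also leaves in a patient whose baseline IgG is above 33.8 BAU/mL but short of an adequate response, for example because of earlier infection or passive antibody.

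If every crossing counts, the error has one direction: response looks faster and more frequent, and a patient boosted by infection during follow-up looks as if vaccine-induced antibody lasted longer. Patients who respond slowly stay at risk of such an event for more visits.

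**Working it through.** **1. The plan's own precision figure.** Table 3 gives a half-width of 9.7 points for 100 events, and the text claims "acceptable precision (half-width of a 95% CI) of about 10% for censoring rates less than 20" percent. With n = 100, S = 0.5 and no censoring, the standard error is √(0.25/100) = 0.05. On the log-log scale it is 0.05/(0.5 × 0.693) = 0.144, and 1.96 × 0.144 = 0.283. The limits are 0.5^exp(0.283) = 0.399 and 0.5^exp(−0.283) = 0.593, so the half-width is 9.7 points, as stated. Simulation with exponential event and censoring times gives 9.88 for 90 events (Table 3: 9.9), 10.14 for 80 (10.2) and 10.51 for 70 (10.6). The sample size figure is sound.

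**2. Possible size for response.** The article gives no rate of infection, antibody use or response, so all rates here are assumptions. Let q be the true vaccine response per 28-day visit and i the proportion of patients still at risk who cross for another reason in the same interval. After k visits:

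- true response = 1 − (1−q)^k
- counted response = 1 − [(1−q)(1−i)]^k
- excess = (1−q)^k × [1 − (1−i)^k]

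For q = 20%, i = 2%, k = 3: 1 − 0.784³ = 51.8% against 1 − 0.8³ = 48.8%, an excess of 3.0 points.

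| q | Day | True | Counted, i = 2% | Counted, i = 4% | Excess (points) |
|---|---|---|---|---|---|
| 10% | 84 | 27.1% | 31.4% | 35.5% | 4.3 and 8.4 |
| 10% | 112 | 34.4% | 39.5% | 44.3% | 5.1 and 9.9 |
| 20% | 84 | 48.8% | 51.8% | 54.7% | 3.0 and 5.9 |
| 20% | 112 | 59.0% | 62.2% | 65.2% | 3.2 and 6.2 |
| 30% | 84 | 65.7% | 67.7% | 69.7% | 2.0 and 4.0 |
| 30% | 112 | 76.0% | 77.9% | 79.6% | 1.9 and 3.6 |

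To judge the assumption: over 13 intervals of 28 days, 2% compounds to 1 − 0.98^13 = 23% and 4% to 1 − 0.96^13 = 41%.

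**3. Possible size for waning.** Assume true waning of w = 5% per interval and a boost in λ = 2% or 4% of patients not yet waned, after which the patient never wanes. That last assumption makes the result an upper bound. With r = (1−λ)(1−w), observed waning after k intervals is (1−λ)w(1−r^k)/(1−r).

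- k = 6: true 1 − 0.95^6 = 26.5%; observed 24.8% and 23.2%.
- k = 12: true 1 − 0.95^12 = 46.0%; observed 40.9% and 36.5%.

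**4. Cost of setting these events apart.** Reading Table 3 with these events as the only censoring, 10, 20 or 30 censored patients give 9.9, 10.2 or 10.6 points against 9.7 with none.

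**The case against.** **The rule may sit elsewhere.** The appendices, the full protocol and any SAP are not shown, and a condensed article commonly leaves censoring rules to them. This stands for the primary end point. A reader might infer from the 847 BAU/mL limit in footnote a of Table 1 that the primary end point is a bare titer threshold, but that footnote governs whether another vaccination visit takes place. For the secondary end points the objection is weaker: their thresholds are printed with no condition on cause.

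**The confounder sentence may mean less than it seems.** It follows remarks on observational design and lack of randomization, so it can be read as no covariate adjustment. Infection after enrollment is an intercurrent event rather than a confounder, and footnote i commits anti-nucleocapsid data to analysis in general terms. A reader might infer that the plan has decided to ignore infection. The text does not go that far. It does acknowledge the effect of infection and states no rule for it.

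**Counting all crossings is legitimate.** In a descriptive study of a titer-guided strategy it answers what happens to patients under that strategy. Censoring at infection has its own bias if patients with waned antibody are infected more often. A reader might infer that the planned analysis is wrong and should be replaced; the documents do not support that. They support a second analysis beside it.

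**Detection is imperfect.** Anti-nucleocapsid IgG is itself an antibody response, in a population that the Introduction says has lower antibody levels after vaccination. After visit 1 no antigen test is scheduled and no infection record is listed. The marker will help to find infections but may miss some. This stands.

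**Conclusion.** The point holds for the secondary response and waning end points. As printed, they attribute every crossing after vaccination to the vaccine, and the visit 1 safeguards do not prevent this. It may hold for the primary end point, subject to Appendices 1 and 3.

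The size is not known. With 2% to 4% non-vaccine crossings per 28 days and 20% true response per visit, counted response is about 3 to 6 points too high by days 84 to 112. It is about 4 to 10 points at 10% true response and about 2 to 4 at 30%. Under the waning assumptions above, cumulative waning is understated by at most about 2 to 3 points at 6 intervals and 5 to 10 at 12.

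Most of these shifts lie inside the planned half-width of about 10 points, but they run one way and would not shrink with more patients. A reader might infer a shift larger than the half-width: at i = 8% and q = 20% the excess is 11 to 12 points. That rate compounds to 1 − 0.92^13 = 66% in 13 intervals, and nothing in the article supports it.

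**What to change.** Before the analysis, prespecify two intercurrent events:

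- new anti-nucleocapsid conversion, with a separate rule for patients positive at baseline (for example a defined rise);
- receipt of a therapeutic anti-SARS-CoV-2 antibody or convalescent plasma, with a fixed look-back window for products given before visit 1.

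Report each response and waning curve twice. The first counts all crossings, as planned. The second treats these events as competing events, using cumulative incidence in place of one minus Kaplan-Meier, or censors at the last visit before the event. A crossing first seen at or after the event does not count as vaccine response in the second curve. Split baseline results by anti-nucleocapsid status. State whether the primary end point follows the same rule.

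This is analysis wording. Both defining variables are already collected, and visits, samples and patient care do not change. The costs are some lost events (half-width 9.7 to about 10.2 points if 20 of 100 patients are censored), possibly informative censoring if the censored version is used, and incomplete detection of infection by anti-nucleocapsid IgG. The last two should be stated with the results.

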### Safety

#### Solicited Adverse Events

In order to evaluate the reactogenicity of COVID-19 vaccinations applied within the SOC [20], this study collects solicited adverse events (AEs) for 7 days (the day of vaccination plus the following 6 days) after each vaccination. As a noninterventional study, this study focuses on solicited AEs only, that is, on a subset of all AEs. Solicited AEs will be collected by the patient using a patient diary. Solicited AEs will be documented starting on the day of each vaccination within the SOC [20] and the following 6 days. The grading system of solicited AEs is based on the Toxicity Grading Scale for Healthy Adult and Adolescent Volunteers Enrolled in Preventive Vaccine Clinical Trials [22] and the Common Terminology Criteria for Adverse Events v5.0 (CTCAE) [23] grading systems (Multimedia Appendix 2).

#### Adverse Drug Reactions

An ADR is defined as a response to a drug that is noxious and unintended and which occurs at doses normally used in humans for prophylaxis, diagnosis, or therapy of disease or modification of physiological function. All ADRs related to one of the COVID-19 vaccines used within the COVID-19 vaccination standard [20] occurring during the study period will be documented in the electronic case report form (eCRF). A serious AE or serious ADR is any untoward medical occurrence that at any dose meets any of the following criteria: (1) results in death, (2) is life-threatening, (3) requires inpatient hospitalization or prolongation of existing hospitalization, (4) results in persistent or significant disability or incapacity, or (5) is a congenital anomaly or birth defect. Serious AEs occurring 7 days (the day of vaccination plus the following 6 days) after each vaccination will be collected in the eCRF.

Serious ADRs occurring during the study period (including the follow-up period) will also be collected in the eCRF.

### Monitoring

The study sites will be monitored to ensure the quality of the data collected. The objectives of the monitoring procedures are to ensure that the subject’s safety and rights as a study participant are respected; that accurate, valid, and complete data are collected; and that the study is conducted in accordance with the study protocol, the principles of Good Clinical Practice (GCP), and local legislation. The exact extent of the monitoring procedures is described in a separate monitoring plan. Monitoring will follow a risk-adapted on-site monitoring strategy. All principal investigators (PIs) agree that the monitor regularly visits the study site and assures that the monitor will receive appropriate support in their activities at the study site, as agreed in separate contracts with each study site. The declaration of informed consent includes a statement allowing the monitor to compare the CRFs with the study subject’s medical records (doctor’s notes, laboratory printouts, etc). The PI will secure access for the monitor to all necessary documentation for study-related monitoring. A monitoring visit report is prepared for each visit describing the progress of the study and any challenges. The PI will reasonably consider the corrective and preventive measures suggested by the monitor. All participant data relating to the study will be recorded on eCRFs. The investigator is responsible for verifying that data entries are accurate and correct by electronically signing the CRF. The investigator must permit study-related monitoring, audits, Research Ethics Committee or National Competent Authority review, and regulatory agency inspections, and provide direct access to source data documents.

### Documentation

PIs will oversee and coordinate data collection, entry, and protection. Study-specific data will be collected by the study staff using designated source documents. Standard GCPs will be followed to ensure accurate, reliable, and consistent data collection. All study data must be verifiable to the source documentation. All source documents will be kept in a locked facility at the study site.

### Data Management

Data management activities will be conducted by the Clinical Trials Centre Cologne (CTCC). The IT infrastructure and data management staff will be provided by the CTCC. The study database will be developed and validated before data entry based on standard operating procedures at the CTCC. The data management system is based on commercial trial software and stores the data in a database. All changes made to the data are documented in an audit trail. The trial software has a user and role concept that can be adjusted on a trial-specific basis. The database is integrated into a general IT infrastructure and safety concept with a firewall and backup system. The data are backed up daily. After completion and cleaning of data, the database is locked and the data are exported for statistical analysis. The data will be entered online at the study sites via the internet. Plausibility checks are run during data entry, thereby detecting many discrepancies immediately. The CTCC data management will conduct further checks for completeness and plausibility and will clarify any questions with the study sites electronically via the trial software. These electronic queries have to be answered by the study site without unreasonable delay. Further details will be specified in the data management manual. A guidance document for data entry in the eCRF will be provided. All participant data relating to the study will be recorded on eCRFs unless transmitted to the sponsor or designee electronically (eg, laboratory data) via secure platform transfer or encrypted email. The investigator is responsible for verifying that data entries are accurate and correct by electronically signing the CRF.

### Archiving

All essential documents according to GCP of the International Council for Harmonisation of Technical Requirements for Registration of Pharmaceuticals for Human Use (ICH-GCP) chapter 8 will be archived for at least 10 years unless longer times are foreseen by local regulatory requirements. No records may be destroyed during the retention period without the written approval of the lead PI of the investigator-initiated trial. No records may be transferred to another location or party without written notification to the lead PI of the investigator-initiated trial. Digitization of paper-based documentation must meet regulatory requirements, especially concerning quality assurance, completeness, and correctness. Paper-based documentation must not be destroyed after digitization and must be archived according to applicable regulations.

### Timelines for the Study Participant

Within a SOC vaccination [20], every patient will receive a varying number of COVID-19 vaccinations. Accordingly, patients will be documented within this study for varying durations depending on the number of vaccine doses needed according to the recent version of the COVID-19 vaccination standard [20] (Table 2).

**Table 2 table2:** Study timeline.

Milestone	Timepoint (quarter)
First patient first visit	Q2 2023
Last patient first visit	Q3 2024
Last patient last visit	Q3 2024
End of study	Q4 2024
Final study report	Q4 2024

